### Data collection and management

The case report form (CRF) designed base on study protocol will be used to record the data. Data collection is performed by trained researchers in accordance with the standardized processing. An electronic research database was established on Research Manager (ResMan) to manage the data. Data entry will be performed by one researcher, and data verification will be carried out by another researcher. (SPIRIT 19).

### Quality control

Every researcher participated in this study will be trained in terms of protocol, CRF, data collection, clinical assessment, and radiological assessment. All radiological data will be measured by two researchers independently, and the final outcome was the average of their measures. The data with major difference between their measures will be measured again, and explain the reason. After the study completed, all data will be checked again. Then the database will be locked after all data are checked and confirmed,. All the original data files will be stored for a period according to corresponding regulations. (SPIRIT 18a).

### Patient and public involvement

Patient and public did not participate in the design, recruitment, conduction of this study.

### Statistical analysis

The demographic characteristics, prognosis factors and treatment factors will be described by using the general statistical description method according to the distribution of the data. Difference in difference analysis of ODI will be used to compare the effectiveness of percutaneous endoscopic decompression group with open decompression and fusion for lumbar spinal stenosis group. The multivariable analysis will be conduct to determine the effect size of treatment factors and potential prognosis factors on outcome. Subgroup analysis will be also conducted to compare the clinical effectiveness of open surgery and endoscopic decompression in patients with different degeneration grades, age, and approaches.

All statistical analyses were conducted using SPSS 25.0 (USA). Statistical significance was accepted at a *p* value of less than 0.05. (SPIRIT 20a).

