### Sample size calculation

The sample size calculation was based on the ODI score at 12 months follow-up. According to the retrospective study of our center and previous literature reported [15], the mean value and standard deviation of ODI score in 12 months after surgery was 20 and 15 in the percutaneous endoscopic decompression group, and 15 and 10 in the open decompression and fusion group. Assuming an overall type 1 error (α) of 0.05 and type II error (β) of 0.1, we needed 137 patients in each group to detect the difference of ODI in two groups. Considering the final follow-up rate of 80% and the center effect value of 1.2, a minimum of 206 patients were needed in each group. Moreover, this study is a real-world observation study, it is necessary to consider confounding factors when analyzing the results. We estimated that 300 patients in each group will be enrolled in this study. (SPIRIT 14).

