### Limitation

The main limitation of this study is that, treatment group in this observational study is clinical routine treatment determined by the shared-decision making between patient and doctor, rather than randomization, which might lead to selection bias. However, the results could be strengthened by the well-designed prospective study, multicenter, large sample size, and the specific inclusion and exclusion criteria [27], and potential confounding factors will be collected for data analysis to minimize the impact of the selection bias.

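### The primary endoscopic-versus-open comparison is a difference-in-differences of ODI with no stated adjustment for confounders or centre, so the plan's commitments on confounding are not tied to the headline estimate

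*Protocol article*

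**What the plan says.** The protocol article's Study population and enrollment section has eligible patients choose their operation after all options are described. The Limitation section accepts that this may cause selection bias. The primary outcome is the change in ODI from baseline to 12 months.

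Two places commit the analysis to dealing with confounding:
- Sample size calculation: "it is necessary to consider confounding factors when analyzing the results". This is the reason given for enrolling 300 per group instead of 206.
- Limitation: "potential confounding factors will be collected for data analysis to minimize the impact of the selection bias".

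The 206 itself already allows for "the center effect value of 1.2".

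Statistical analysis then names the method for the group comparison: "Difference in difference analysis of ODI will be used to compare the effectiveness of percutaneous endoscopic decompression group with open decompression and fusion". The next sentence announces a multivariable analysis of treatment factors and potential prognostic factors, without saying which outcome it models. Exposure measures defines treatment factors as operation approach, operative time, blood loss, postoperative hospital stay and surgeon.

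**The concern.** The operations are chosen, not allocated, so patients who pick endoscopic surgery may differ from those who pick open fusion in ways that also affect recovery. Stenosis grade, previous spinal surgery, comorbidity, age and treating centre are plausible examples.

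Difference-in-differences subtracts any gap in ODI that would have stayed the same without a treatment difference. It does not deal with factors that alter the amount of improvement. Its key assumption is that both groups would have improved equally under the same treatment. Table 1 has a single pre-operative ODI, so there is no earlier trend against which to check this.

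At stake is what the headline result means. Followed as written, it could mix treatment effect and case mix, while the extra patients recruited on account of confounding serve an adjustment that the named primary method does not mention.

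**Working it through.** **1. The plan's own sample size reproduces.** Inputs, all from Sample size calculation: "the mean value and standard deviation of ODI score in 12 months after surgery was 20 and 15 in the percutaneous endoscopic decompression group"; "15 and 10 in the open decompression and fusion group"; two-sided α 0.05 (sidedness is not stated, but one-sided gives 112 and does not match); power 90%.

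- n = (15² + 10²) × (1.960 + 1.282)² / 5² = 325 × 10.507 / 25 = 136.6, rounded up to 137. The plan has 137.
- Inflation: 137 × 1.2 / 0.80 = 205.5, rounded up to 206. The plan has 206.

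There is no arithmetic error here.

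**2. Room that 300 per group leaves for adjustment.**

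- Effective number per group: 300 × 0.80 / 1.2 = 200.
- SE = √(325/200) = 1.275. Power = Φ(5/1.275 − 1.96) = 97.5%.
- Tolerable variance inflation: 200 / 137 = 1.46. This corresponds to covariates explaining about 1 − 137/200 = 31% of the variation in treatment choice.

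These figures use the SDs of 12-month scores, as the plan does, whereas the primary outcome is a change score. If the baseline SD were 15 and the baseline-to-12-month correlation 0.3 (both assumed), the variances of change would be:
- endoscopic: 225 + 225 − 2 × 0.3 × 15 × 15 = 315 (SD 17.7)
- open: 225 + 100 − 2 × 0.3 × 15 × 10 = 235 (SD 15.3)

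The sum is 550, the required n is 550 × 10.507 / 25 = 231.2, so 232 effective per group, and power at 200 is about 85%. The 1.46 therefore holds only on the plan's own inputs.

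**3. Does the multivariable analysis supply the adjusted contrast?** Setting the sections side by side:
- Aim and objective makes prognostic factors the secondary aim, and Secondary outcome measures lists the relation of exposure measures to clinical outcomes. The multivariable sentence matches these, not the primary outcome.
- The outcome it models is not named.
- Operative time, blood loss and hospital stay are consequences of the operation. Adjusting the group contrast for them would distort it.
- Operation approach could mean endoscopic versus open, or transforaminal versus interlaminar (the Treatment section uses the word for the latter pair). It is not certain that the model contains the primary contrast.

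**4. Hypothetical size of bias.** None of the bias inputs below is in the documents.

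- *Unbalanced prognostic factor.* Bias = prevalence difference × effect on ODI change. With 10 to 30 percentage points and 3 to 10 ODI points, this runs from 0.10 × 3 = 0.3 to 0.30 × 10 = 3.0 points.
- *Baseline ODI imbalance.* The gap between the change-score and baseline-adjusted estimates is (1 − slope) × imbalance. With an imbalance of 2 to 8 points and slopes of 0.2 to 0.6, it runs from 0.4 × 2 = 0.8 to 0.8 × 8 = 6.4 points.
- *Effect on the error rate.* P(reject) = 1 − Φ(1.96 − bias/SE) + Φ(−1.96 − bias/SE), with no true difference and 300 × 0.80 = 240 analysed per group. The first SE, √(325/240) = 1.164, ignores the centre effect. The second, √(325/200) = 1.275, includes it. The third, √(550/200) = 1.658, also uses the assumed SDs of change.

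| Bias (ODI points) | SE 1.164 | SE 1.275 | SE 1.658 |
|---|---|---|---|
| 1 | 14% | 12% | 9% |
| 2 | 40% | 35% | 23% |
| 3 | 73% | 65% | 44% |

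**The case against.** The strongest reply is that the text does not call the comparison unadjusted. A difference-in-differences is often fitted as a regression with covariates, and this is a condensed article whose analysis plan is not shown. The covariate list, the form of the centre term and any weighting scheme may sit there, and their absence here is no finding. This stands. A reader might infer that the primary analysis is definitely unadjusted, but the documents do not say so. What they show is a named primary method to which the stated commitments on confounding are not attached.

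A second reply is that the multivariable analysis estimates the effect of treatment factors, with operation approach listed first, so an adjusted treatment effect may be planned. That reading is possible, but the sentence is too ambiguous to settle the matter, and its variable list would be unsuitable for the primary contrast.

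A third concerns regression to the mean. A reader might infer that any baseline ODI imbalance becomes a spurious difference in change. This is not so. If the groups differ stably and parallel trends hold, the change score is unbiased and adjusting for baseline ODI introduces bias (Lord's paradox). The 0.8 to 6.4 points above are a gap between two estimators, and a bias only if the baseline-adjusted model is right. The documents cannot say which model is.

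Finally, the error rates depend wholly on assumed imbalances. Small imbalances would give small distortions.

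**Conclusion.** The point holds as a defect in how the primary comparison is specified. Treatment is self-selected, the plan says confounding must be handled and enlarges the sample on that account, and the one method named for the effectiveness comparison carries no stated confounder or centre adjustment. Difference-in-differences does not by itself supply it, and the multivariable analysis does not clearly do so.

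The size of the resulting bias is unknown. The illustrations show that a bias of 2 points, 40% of the planned 5-point difference, would be serious for the error rate. They do not show that such a bias exists. The planning figures of 137 and 206 are correct.

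Because this choice determines the headline result of a non-randomised comparison, it should be settled in writing before the database is locked.

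**What to change.** In Statistical analysis, state that the primary contrast in ODI change to 12 months is adjusted, by regression or propensity-score weighting, for centre and for pre-operative variables in Table 1: age, gender, BMI, comorbidity, smoking, previous spinal surgery, pathology type, affected level, symptom duration, degeneration grade and stenosis grade. State that intra- and post-operative variables (operative time, blood loss, hospital stay) are excluded from this model.

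Describe the prognostic multivariable analysis separately and name its outcome. Report the plain difference-in-differences and a version adjusted for baseline ODI as sensitivity analyses. Presenting both shows how far the answer depends on the assumption about baseline differences. If an unshown analysis plan already does this, a sentence in the protocol pointing to it is enough.

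The cost is wording and modest analysis work. The listed covariates are already collected before surgery, and the treating centre is known for every patient. Standard errors may widen; the plan's own inputs leave room for an inflation of about 1.46, less if ODI change varies more than 12-month ODI. Adjustment also handles measured factors only, so the selection-bias caveat in Limitation should stay.

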## Background

Lumbar spinal stenosis (LSS) is caused by the degeneration of the lumbar spine including disc herniation, the hypertrophy of facet joint and ligamentum flavum, and the formation of osteophyte [1]. The characteristics of LSS are low back pain, sciatica, and intermittent claudication which will seriously affect the daily life and work of patients [1, 2].

LSS is the most frequent indication for spine surgery among the elderly population [3, 4], and previous studies have demonstrated that surgical treatment was better than conservative treatment in selected patients [5, 6].

Open decompression and fusion was the most common treatment and used to be regarded as the golden standard treatment for LSS [7, 8]. However, due to the surgical trauma caused by open decompression and fusion surgery, complications, and the acceleration of adjacent level degradation, more minimally invasive treatments were required [9–11].

Percutaneous endoscopic decompression is a minimally invasive treatment which has the advantage of operated under local anesthesia, less surgical trauma, fewer complications, shorter hospital stay, and rapid postoperative recovery. The application of percutaneous endoscopic decompression has been limited to soft disc herniation. In recent years, with the development of endoscopic instruments and surgical techniques, some surgeons applied percutaneous endoscopic decompression for the treatment of LSS [12–14]. However, the related studies had some limitations including small sample size, short-term follow-up, single-center, no control group, retrospective study which reduced the quality of evidence for the conclusion. (SPIRIT 6a,b).

The present prospective, multicenter, large sample size cohort study based on real-world will be helpful for the evaluation of the clinical effectiveness and safety of the percutaneous endoscopic decompression for LSS. Furthermore, we designed to analyze various influence factors for the prognosis of LSS including degeneration grade, pathology type, stenosis grade, decompression range. The present study will provide useful information for the development of guidelines and standards for percutaneous endoscopic decompression for the treatment of LSS.

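### The subgroup analysis by age and degeneration grade is described only as open versus endoscopic comparisons under a general p<0.05 rule, which does not test whether the treatment effect differs between subgroups

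*Protocol article*

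**What the plan says.** All of this is in the Statistical analysis section of the protocol article.

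- Main comparison: "Difference in difference analysis of ODI will be used to compare the effectiveness" of the two operations.
- Subgroups: a single sentence, "Subgroup analysis will be also conducted to compare the clinical effectiveness of open surgery and endoscopic decompression in patients with different degeneration grades, age, and" surgical approaches. It gives no cut-points, model or rule for reading the subgroup results against each other.
- Threshold: "Statistical significance was accepted at a *p* value of less than 0.05". This covers every analysis and is not specific to the subgroups.
- Multivariable analysis: described as estimating how treatment and prognostic factors affect outcome. It does not mention whether the effect of the operation varies with a patient characteristic.

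Under Radiological assessment, disc degeneration is graded on MRI by Pfirrmann grade, at both the operated and the adjacent level.

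**The concern.** A test of open against endoscopic surgery inside one subgroup has the null hypothesis of no difference between the operations in those patients. The usual reason to split by age or degeneration grade is to learn whether the relative effect depends on them. The null for that question is an equal difference in every subgroup.

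The two questions come apart once the operations truly differ, and the Sample size calculation section assumes that they do (12-month ODI of 20 against 15). With a common non-zero effect, whether a subgroup reaches significance depends largely on how many patients it holds.

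A result such as open surgery better in high-grade degeneration and no difference in low-grade could then appear when the relative effect is the same in everyone. The Background says: "The present study will provide useful information for the development of guidelines and standards for percutaneous endoscopic decompression". In that setting, a pattern produced by subgroup size could be read as guidance on patient selection.

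**Working it through.** **Inputs from the Sample size calculation section.** "standard deviation of ODI score in 12 months after surgery was 20 and 15 in the percutaneous endoscopic decompression group"; the open group is given mean 15 and SD 10. The error rates are "Assuming an overall type 1 error (α) of 0.05 and type II error (β) of 0.1". Planned enrolment is 300 per group, with 80% follow-up and a center-effect factor of 1.2.

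**Reproducing the plan's figure.** With n per group = (15² + 10²)(1.960 + 1.282)² / 5², the result is 325 × 10.507 / 25 = 136.6, rounded up to 137. This matches the article with a two-sided α. Inflation gives 137 × 1.2 / 0.8 = 205.5, rounded up to 206, which also matches.

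**Assumptions added here.**
- The true ODI difference is 5 points in every subgroup.
- There are 300 × 0.80 = 240 completers per group.
- The two groups are equally represented within each subgroup, and there is no confounding.
- The SDs of the 12-month score stand in for the SD of change, which the article does not give.
- Subgroup sizes are not in the article, so a range is shown.

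**Power within a subgroup.** For n patients per group in a subgroup, SE = √(325/n) and power = Φ(5/SE − 1.960). The other tail is negligible.

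**Discordance.** For independent subgroups, the chance that some but not all are significant is 1 − (product of powers) − (product of 1 − power).

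| Split (assumed) | n per group | SE | Power | Some but not all significant |
|---|---|---|---|---|
| 50/50 | 120, 120 | 1.65, 1.65 | 0.86, 0.86 | 24% |
| 30/70 | 72, 168 | 2.12, 1.39 | 0.65, 0.95 | 36% |
| 20/80 | 48, 192 | 2.60, 1.30 | 0.48, 0.97 | 51% |
| three equal | 80 each | 2.02 each | 0.70 each | 63% |
| 30/45/25 | 72, 108, 60 | 2.12, 1.73, 2.33 | 0.65, 0.82, 0.57 | 67% |

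Worked example for 50/50: 5/1.646 − 1.960 = 1.078, so power is 0.86. Discordance is 2 × 0.8595 × 0.1405 = 0.24.

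**With the article's center effect.** Dividing 240 by 1.2 leaves an effective 200 per group. The first four rows become 33%, 44%, 57% and 71%.

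**If the operations do not differ at all.** Two subgroups give discordant verdicts in 2 × 0.05 × 0.95 = 9.5% of studies.

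**Interaction test.** Under equal effects it rejects in 5% of studies by construction. For equal halves, the SE of the difference between the two subgroup effects is √(2 × 325/120) = 2.33. Power for a 5-point difference in effect is Φ(5/2.327 − 1.960) = 0.57, or 0.50 with the effective 200 per group. For an 8-point difference it is 0.93 with 240 per group.

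**The case against.** The strongest reply is that the article does not commit the error. A reader might infer that the plan will judge effect modification by setting one subgroup's p-value against another's. The text does not say so. The subgroup sentence names no test, the 0.05 threshold stands in a separate paragraph and applies to everything, and nothing rules out a group-by-factor term. The article is condensed and any analysis plan is not shown, so a missing interaction test would not by itself be a finding. This stands, and it limits what can be claimed. What remains is that the contrast the article does state is operation against operation in patients of each type. An analysis that followed it literally would never compare the effects.

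A reader might also infer that spurious subgroup differences are likely. That goes too far. With two equal halves the rate is about one in four, or one in three with the center effect. Without the center effect it passes one half only near a 20/80 split or with three strata. All these figures also depend on a reading rule that the article does not state.

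It can further be said that effect modification is not among the listed objectives, and that the Background's remark on guidelines concerns the whole study, not the subgroup results. Both are true, so harm to patient selection is a possibility and not a documented consequence. The primary comparison and the sample size are unaffected.

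Finally, the study is not randomized, and its Limitation section acknowledges selection bias. An unadjusted interaction can be biased as well, and its 5% error rate holds only without confounding. This stands too, and the remedy has to allow for it.

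**Conclusion.** The point holds as a correction to the described method. For age and degeneration grade, the article sets out treatment comparisons within subgroups under a general 0.05 rule and nowhere compares the effect between subgroups. Such comparisons cannot show whether the relative effect differs.

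If a difference were inferred from discordant significance, an identical 5-point effect would produce that pattern in about 24% to 67% of studies over the splits examined, against 5% for an interaction test. These rates rest on the article's SDs, 240 completers per group, no confounding and assumed subgroup sizes.

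The point does not extend to surgical approach. If that word means transforaminal versus interlaminar, it exists only in the endoscopic group and no group-by-approach interaction can be estimated.

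**What to change.** Replace the subgroup sentence, for age and degeneration grade, with one stating that:

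- subgroup differences will be judged by a group-by-factor interaction in a model for ODI change from baseline to 12 months, fitted to all analyzed patients and adjusted for the same confounders as the main comparison;
- the difference between operations in each subgroup will be reported with its 95% confidence interval;
- these analyses are exploratory.

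Entering age as continuous and degeneration grade as an ordinal term would be sensible but is not essential. The text should also say at which spinal level the grade is taken, since both operated and adjacent levels are graded.

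The cost is a sentence or two and one interaction per factor, using data already collected. The downside is modest power: about 57% for a 5-point difference in effect between equal halves. Fewer subgroup claims will be made, and a non-significant interaction should not be presented as proof that the effect is the same in everyone.

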### Missing data

At the final complete analysis for the primary outcome, we will exclude the cases which missing ODI data at 12 months follow-up [26]. Missing data could influence the validity of prospective studies, we will aim to maximize the follow-up rate to above 80%. (SPIRIT 20c).

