### Follow up

Patients will be followed up at 3, 6, 12 months after surgery. Clinical and radiological assessment at 3 and 12 months after surgery will be performed through outpatient follow-up. Clinical assessment at 6 months after surgery will be completed through email or telephone (Table 1). Adverse events will be recorded during the follow-up period. (SPIRIT 13, 18b).

**Table 1 Tab1:** Data collection

Variables	Baseline	Perioperative	3 months	6 months	12 months
Demographic Variable					
Age	X				
Gender	X				
BMI	X				
Ethnicity	X				
Center of residence	X				
Risk Factors					
Comorbidity	X				
Smoking status	X				
Previous spinal surgery	X				
Pathology types	X				
Affected level	X				
Symptoms duration	X				
Degeneration grade	X				
Stenosis grade	X				
Treatment Factors					
Operation approach		X			
Operative time		X			
Bleed loss		X			
Postoperative hospital stay		X			
Surgeon		X			
Radiological Assessment					
X-ray	X		X		X
CT	X		X		X
MRI	X		X		X
Clinical Assessment					
VAS (back & leg)	X	X	X	X	X
ODI	X		X	X	X
JOA	X		X	X	X
MacNab criteria			X	X	X
Patient satisfaction		X	X	X	X
Complications		X	X	X	X

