### Outcome measures

#### Primary outcome measure

The primary outcome measure is the score changes of ODI between baseline and 12-month follow-up.

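### The primary analysis excludes every patient without a 12-month ODI although ODI is also scheduled at 3 and 6 months; if loss depends on early response, the primary difference is biased by an unknown amount

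*Protocol article*

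**What the plan says.** The Missing data section fixes the rule for the primary outcome: "we will exclude the cases which missing ODI data at 12 months follow-up". It accepts that missing data can affect validity, and its one named response is to aim for follow-up above 80%.

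The outcome is a change score: "The primary outcome measure is the score changes of ODI between baseline and 12-month follow-up". The Statistical analysis section says that "Difference in difference analysis of ODI will be used to compare the effectiveness" of the two operations.

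The Follow up section states that "Patients will be followed up at 3, 6, 12 months after surgery", and Table 1 marks ODI at baseline and at all three of these visits. The way of collection differs. "Clinical assessment at 6 months after surgery will be completed through email or telephone", whereas "Clinical and radiological assessment at 3 and 12 months after surgery will be performed through outpatient follow-up".

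The Sample size calculation section builds in loss: "Considering the final follow-up rate of 80" per cent, together with a centre effect of 1.2. Study population and enrollment says that patients choose their own operation.

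**The concern.** Complete-case analysis of the change score is sound if loss is unrelated to the 12-month result, given what the analysis conditions on. Here the analysis can condition on group and baseline variables, but the likeliest driver of loss that is actually recorded is how the patient was doing at 3 and 6 months. Difference in difference removes baseline imbalance, and baseline covariates adjust for baseline risk. Neither corrects loss driven by early postoperative response.

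The schedule makes the relevant patients likely to exist. The 6-month score can be given remotely and the 12-month assessment is a clinic visit, so some patients will have the first and not the second. Treatment is self-chosen and the two operations are very different, so an equal loss process in the two groups cannot be presumed. At stake is the primary estimate. The 80% allowance protects power and does nothing for bias.

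**Working it through.** **The plan's own figure.** Inputs from Sample size calculation: 12-month mean and SD of 20 and 15 (endoscopic) and 15 and 10 (open), α 0.05, β 0.1. Two-sided:

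n = (15² + 10²) × (1.960 + 1.282)² / 5² = 325 × 10.51 / 25 = 136.6, so 137 per group.

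Inflation: 137 × 1.2 / 0.8 = 205.5, so 206. Both stated figures reproduce.

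**Power is not the issue.** With 300 enrolled and 20% lost, 300 × 0.8 = 240 per group remain, against 137 × 1.2 = 164.4 needed. The question is bias only.

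**Size of the bias on the planned endpoint.** From the protocol: the means and SDs above and 20% loss per group. Assumed, because the documents give no values:
- correlation of 6- and 12-month ODI 0.7;
- equal mean baseline ODI in the groups, baseline SD 15;
- baseline correlated r = 0.2 to 0.5 with the postoperative scores;
- log-odds of loss linear in standardised 6-month ODI, z, with slope 0.5, 1.0 or 1.5 per SD.

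The true difference in change is then 20 − 15 = 5.0.

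*Step 1.* Let p(z) be the probability of loss, with its intercept set so that average loss is 20%. The mean of z among retained patients is s = E[z(1 − p)] / 0.8. Numerical integration gives s = −0.096, −0.173 and −0.227 for the three slopes. The corresponding loss below and above the median 6-month score is about 14% and 26%, 9% and 31%, and 6% and 34%.

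*Step 2.* Selection on z moves the retained 12-month mean by SD × 0.7 × s and the retained baseline mean by 15 × r × s. The mean change therefore moves by s × (SD × 0.7 − 15r):
- endoscopic: 15 × 0.7 = 10.5, so s × 7.5 at r = 0.2 and s × 3.0 at r = 0.5;
- open: 10 × 0.7 = 7.0, so s × 4.0 at r = 0.2 and s × (−0.5) at r = 0.5;
- same dependence in both: the baseline terms cancel, leaving s × (10.5 − 7.0) = s × 3.5.

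*Step 3.* Complete-case difference, truth 5.0. Example for slope 1.0, endoscopic only, r = 0.2: 5 − 0.173 × 7.5 = 3.70.

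| Slope per SD | Endoscopic only (r 0.2 / 0.5) | Open only (r 0.2 / 0.5) | Same in both |
|---|---|---|---|
| 0.5 | 4.28 / 4.71 | 5.38 / 4.95 | 4.66 |
| 1.0 | 3.70 / 4.48 | 5.69 / 4.91 | 4.39 |
| 1.5 | 3.30 / 4.32 | 5.91 / 4.89 | 4.21 |

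Simulation of the same model agrees to within about 0.1 point. Predicting the change from 6-month ODI for all patients returns about 5.0 in every cell.

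**The case against.** Several points on the other side stand.

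- *Differential loss is not documented.* No section gives loss by group or by early response. The 20% is a planning allowance, and the Missing data section aims to do better. The existence of the rule is certain; a material bias is not.
- *The largest figures need one-sided, strong dependence.* A slope of 1.5 means roughly 3% loss one SD below the mean 6-month score and 40% one SD above, in one group only. When both groups behave alike, the shift is 0.3 to 0.8 points, and it arises because the planned SDs differ (15 against 10).
- *A reader might infer that about half of the planned difference could vanish.* Working with the 12-month score alone, endoscopic-only dependence gives 5 + 10.5 × s, or about 4.0, 3.2 and 2.6. The documents do not support using those figures: the endpoint is change from baseline, and patients with poor early scores tend to start higher, so part of the shift cancels. Nor do they support a fixed direction, since the open-only case mostly raises the difference.
- *The return to 5.0 is built in.* Loss was made to depend only on a 6-month score that every patient had. Patients lost before 6 months, or because of something that happened after it, are not covered.
- *The article condenses a fuller plan.* Sensitivity analyses or imputation details may be set out elsewhere, and their absence here is no fault. The deletion is also confined to the primary outcome, so these patients are not removed from the secondary outcomes.

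What remains is that the article does state the primary rule, and that rule sets aside the recorded scores most likely to inform the missing one.

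**Conclusion.** The point holds as a conditional weakness in a stated rule. Complete-case deletion is a poor primary choice when ODI is scheduled at two earlier postoperative visits. If loss depends on early response, the primary difference is biased, and the documents do not allow its size or direction to be known.

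Under the assumptions listed, a true 5.0 becomes about 3.3 to 4.7 (endoscopic-only dependence; separate simulation runs put the lower end at 3.2 to 3.3), about 4.9 to 5.9 (open-only) or about 4.2 to 4.7 (same in both). These figures are illustrations and do not predict what the study will find. The stated sample size is correct and power is adequate. This is an improvement that should be made because it is cheap, and it does not invalidate the design.

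**What to change.** Replace the rule in the Missing data section. The primary 12-month contrast should include all patients with a baseline ODI and at least one postoperative ODI, by one of two routes fixed in advance:

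- a linear mixed model for repeated measures on ODI at baseline, 3, 6 and 12 months, with group, time, group × time and the planned covariates, reporting the group difference in change at 12 months; or
- multiple imputation of 12-month ODI within group from baseline, 3- and 6-month ODI and baseline covariates, followed by the planned difference-in-difference comparison.

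Keep the complete-case analysis as a sensitivity analysis. A further analysis that shifts the imputed values by group, for loss not explained by observed scores, is useful but optional.

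Cost: revised wording before the database is locked and slightly more analysis work; the planned software fits mixed models. The sample size is unchanged, and no new data or patients are needed. The price is reliance on loss being explained by observed data, which should be stated with the result.
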